#### Sample size

2.5.2

The total sample size was 76 cases and they are randomly divided into 2 groups. According to the trial design, the sample size estimation method used a completely random design sample rate and the population rate comparison. The sample size is calculated according to the following formula: $\text{n}=\pi_{0}\left(1-\pi_{0}\right){\left\{\frac{{\text{z}}_{\alpha }+{\text{z}}_{\beta }}{\delta }\right\}}^{2}$. Through literature study on ordinary acupuncture treatment for acne patients, the average effective rate was 76.7%, so the overall rate of Group A was *π*_0_ = 76.7%. Combined with clinical experience, the total effective rate of SSGA in treating acne is 98.48%, then the overall rate of expected test results was *π* = 98.48%. One-sided cutoff of this trial: z_α_ = 1.645, z_β_ = 1.282, δ=*π*-*π*_0_ = 0.9848-0.767 = 0.2178. Enter the formula to get the estimated sample content value n≈32. Considering that “dropping” may increase the sample size by up to 20%, the sample size was estimated to be 38 cases. Finally, Group A and Group B are according to the random number table method.

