### Study design and ethics

2.1

The proposed study is a prospective, parallel, two-armed randomized controlled trial using a 1:1 allocation ratio with a 4-week follow-up. The study will be conducted at Dongzhimen Hospital of Beijing University of Chinese Medicine and the Third Affiliated Hospital of Henan University of Traditional Chinese Medicine. The outline of the study patient process is in Figure 1.

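### The 76 patients are justified by a one-sample, one-sided formula that does not fit a two-arm χ² comparison; the implied 90% power holds only under particular choices of sidedness, χ² variant and loss

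*Protocol article*

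**What the plan says.** Section 2.5.2 (Sample size) gives the method as "the sample size estimation method used a completely random design sample rate and the population rate comparison" and prints n = π0(1−π0){(z_α+z_β)/δ}². The inputs are a literature rate for ordinary acupuncture ("the average effective rate was 76.7" per cent), an expected rate for the test method ("the total effective rate of SSGA in treating acne is 98.48" per cent), their difference δ = 0.2178, and "One-sided cutoff of this trial: z_α_ = 1.645, z_β_ = 1.282". The result is about 32. The allowance for dropping out is that this "may increase the sample size by up to 20%, the sample size was estimated to be 38 cases", and the total is 76.

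Section 2.1 describes a "prospective, parallel, two-armed randomized controlled trial using a 1:1 allocation ratio". Section 2.5.1 compares Group A with Group B on the primary outcome by a χ² test and sets P<.05 as the limit of significance. It does not say whether the test is one- or two-sided, or whether the χ² is corrected.

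Section 2.5.2 also introduces the 76.7% with the words "so the overall rate of Group A was", although sections 2.3.1 and 2.3.2 make Group A the SSGA arm and Group B the conventional-acupuncture arm.

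**The concern.** The printed formula has one variance term, π0(1−π0). It is the size for comparing one sample with a fixed, known rate. Here the control rate will be estimated from a randomised arm of the same size, so its sampling error belongs in the calculation. The sidedness also fails to match: 2.5.2 declares a "One-sided cutoff of this trial", whereas an ordinary χ² test at P<.05 is non-directional and 2.5.1 states no one-sided version.

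This calculation is the only justification given for 76 patients. If it stands, a non-significant result may be read as coming from a trial with 90% power for the assumed difference. The abstract says the results will feed the sample size of later large studies, so that misreading would carry forward.

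**Working it through.** **Inputs (section 2.5.2).** π0 = 0.767; π1 = 0.9848; δ = 0.2178; z_α = 1.645; z_β = 1.282 (90% power; the percentage itself is not printed). Variances: 0.767 × 0.233 = 0.17871 and 0.9848 × 0.0152 = 0.01497, sum 0.19368. Mean rate 0.8759, so 2 × 0.8759 × 0.1241 = 0.21740.

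**1. The plan's own figure.** 0.17871 × (2.927/0.2178)² = 0.17871 × 180.605 = 32.28, printed as 32. Then 32 × 1.2 = 38.4, printed as 38, and 2 × 38 = 76. The figures reproduce, each rounded down. The fault lies in the choice of formula, not in the arithmetic.

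**2. Two-sample size at the same rates and 90% power, evaluable per group.**
- Unpooled, n = (sum of variances)(z_α+z_β)²/δ². One-sided: 0.19368 × 180.605 = 34.98, so 35. Two-sided (1.96): 0.19368 × (3.242/0.2178)² = 42.91, so 43.
- Pooled under the null, n = [z_α√0.21740 + z_β√0.19368]²/δ². One-sided: [1.645 × 0.46626 + 1.282 × 0.44009]²/0.2178² = 37.36, so 38. Two-sided: 46.05, so 47.

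All four exceed 32.

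**3. Power of the planned trial.** A 20% loss from 38 leaves 38 × 0.8 = 30.4, taken as 30. The normal approximation is Φ{[δ√n − z_α√0.21740]/√0.19368}. For example, two-sided at n = 30: (1.1929 − 0.9139)/0.4401 = 0.634, giving 73.7%. Exact power is obtained by summing the binomial probabilities of all outcome pairs that the test rejects.

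| Test | 38 per group | 32 | 30 |
|---|---|---|---|
| Two-sided uncorrected χ², exact | 92.0% | 86.4% | 83.7% |
| Two-sided Fisher, exact | 78.7% | 65.3% | 59.6% |
| Two-sided continuity-corrected χ², exact | 77.3% | 65.3% | 59.6% |
| Two-sided, normal approximation | 83.5% | 76.5% | 73.7% |
| One-sided uncorrected (1.645), exact | 95.8% | 92.9% | 91.3% |
| One-sided, normal approximation | 90.5% | 85.5% | 83.3% |

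**4. Why the χ² variant matters.** At 30 per group the expected number of non-effective cases is 30 × 0.1241 = 3.7 per arm under the pooled rate. With counts below 5, an analyst may well turn to Fisher's test or a correction, and at that size the choice moves power from 84% to 60%.

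**5. Dropout.** If 20% loss is meant, 32/0.8 = 40 per group, or 33/0.8 = 41.25, so 42, when 32.28 is first rounded up. The planned 38 leaves 30.4, below the plan's own 32.

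**The case against.** A reader might infer that the trial has 74% power and cannot deliver 90%. The documents do not support that as a flat statement.

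- Two-sidedness is inferred. Section 2.5.1 states no sidedness, and the only explicit statement, in 2.5.2, is one-sided. An uncorrected test at that cutoff has exact power of 91% even at 30 per group.
- The 74% is a normal approximation with one rate at 98.48%, where about 0.5 failures are expected among 30 (30 × 0.0152). For a two-sided uncorrected χ² the exact figure is 84%, and with no loss it is 92%.
- The 60% applies only under Fisher's test or a continuity correction, and the protocol names neither.

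These points stand, and they make the shortfall conditional. They do not rescue the calculation: the formula omits the second arm's variance under either sidedness, and a one-sided analysis appears nowhere in 2.5.1.

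The trial is also presented as a feasibility and preliminary-efficacy study, and its limitations section admits a small sample. That lowers the stakes, but the plan still chose a power calculation to justify its size and still plans a between-group significance test.

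The dropout point is small. The wording can be read literally as multiplying by 1.2, and the gap is 38 against 40 (or 42) per group. The Group A label is a slip without numerical effect, since the same paragraph ties 76.7% to ordinary acupuncture and 98.48% to SSGA.

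**Conclusion.** The concern holds in this form: the sample-size method is for a different design from the one being run, and its sidedness is not matched in the analysis section. At the protocol's own rates and 90% power, the two-sample requirement is 43 to 47 evaluable per group two-sided, or 35 to 38 one-sided, against 32.

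Whether 90% power is reached depends on choices the protocol leaves open. For a two-sided test, exact power after 20% loss is about 84% uncorrected and about 60% with Fisher's test or a continuity correction. With no loss it is 92% and 77 to 79% respectively. Only a one-sided uncorrected test stays above 90% at 30 per group.

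These figures assume that 76.7% and 98.48% are correct, that loss is equal in both arms, and that the outcome compared is an effective/not-effective proportion. On the last point, section 2.4.1 defines the primary outcome as change in IGA score, and the article gives no definition of an effective case. Any restated power is therefore tied to a binary outcome that still has to be defined.

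**What to change.** In 2.5.2, replace the one-sample formula with the two-proportion formula. State one sidedness, and make 2.5.1 say the same. Name the χ² variant (uncorrected, continuity-corrected or Fisher).

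Keep 76 patients and restate the power for the named test in place of the implied 90%. Suggested wording for a two-sided uncorrected χ²: with 38 randomised per group and 30 evaluable after 20% loss, exact power to detect 76.7% versus 98.48% is about 84%. If Fisher's test or a continuity correction is chosen, the figure is about 60%. State the definition of an effective case to which the figure refers.

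Two minor corrections belong in the same paragraph. If 20% loss is meant, inflate by n/(1−0.20) and round up; otherwise say that the allowance is n × 1.2. Label π0 as the Group B rate.

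The cost is a rewritten paragraph, one added clause in 2.5.1 and a less favourable power figure under two-sided testing with loss. No additional patients are required.

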**Methods::**

The proposed protocol is planned as a randomized, assessor-blind, conventional-treatment-controlled trial to evaluate the efficacy of SSGA on gastrointestinal damp-heat acne. Seventy six gastrointestinal damp-heat acne patients will be randomly divided into 2 groups and receive SSGA or conventional acupuncture treatment. The entire study period is 12 weeks, including an 8-week treatment period and a 4-week follow-up period. All patients will receive 16 sessions of acupuncture treatment over 8 weeks. The primary outcome is the investigation global assessment (IGA) at week 8, which is an overall assessment of the degree of the inflammatory and non-inflammatory lesion. The secondary outcomes include IGA, the total facial lesion count (Total Lesion Count), the acne-specific quality of life, etc at weeks 8 and 12. The Expectation and Credibility of treatment rating scale will be used to measure the patients’ attitudes to acupuncture after the first treatment. Adverse events will also be recorded.

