#### Primary outcome

2.4.1

The primary outcome measurement will be expressed by the change in IGA score from baseline to the end of 8-week treatment. The IGA score is an overall assessment of the degree of inflammatory and non-inflammatory lesions and is divided into 6 levels.^[21,22]^

Grade 0 (0 points): the skin is smooth and clean, without any inflammatory or non-inflammatory lesions; Grade 1 (1 point): the skin is almost smooth, non-inflammatory lesions are rare, and no more than 1 small inflammatory lesion; Grade 2 (2 points): mild, with some non-inflammatory lesions, and only a few inflammatory lesions (only papules or pustules, no nodular lesions); Grade 3 (3 points): moderate, there are multiple non-inflammatory lesions, and there may be some inflammatory lesions, but no more than 1 small nodular lesion; Grade 4 (4 points): severe, with multiple non-inflammatory and inflammatory lesions, but only a few nodular lesions; Grade 5 (5 points): extremely severe, with multiple non-inflammatory and inflammatory lesions, and multiple nodular cystic lesions.

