#### Secondary outcome measurements

2.4.2

The secondary measurements will be measured by changes in IGA, total facial lesion counts (Total Lesion Counts),^[21,23]^ inflammatory lesion counts, non-inflammatory lesion counts,^[21]^ and Acne-Specific Quality of Life^[24]^ at 8 and 12 weeks compared with baseline display.

Total lesion count includes inflammatory lesion counts and non-inflammatory lesion counts. Inflammatory lesions include inflammatory papules, pustules, cysts, and nodules. Non-inflammatory lesions include blackheads and whiteheads. Lesions will be evaluated on the forehead, cheeks, nose, and chin.

Acne-specific quality of life has 14 items in total, covering 3 areas, including self-perception, social function, and emotional function.^[24]^ This scale is mainly used to test the quality of life of patients with skin diseases. Each item is divided into 4 levels according to the specific conditions of the patient, with a score of 0 to 3. The total score of 16 items is the patient's skin disease quality of life score. The total index score is 30 points. The higher the score, the worse the patient's quality of life.

The Expectation and Credibility of treatment rating scale will be used to measure the patients’ attitudes to acupuncture after the first treatment. The patients will be asked the following question: “Do you think SSGA will be effective in treating the symptoms of ance?”

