#### Clinical data analysis

2.5.1

Statistical analysis of all data will use IBM SPSS statistical version 24.0 software (IBM Corporation, Armonk, New York). For continuous variables, the data will be represented by the mean (standard deviation) or median (interquartile range) according to the normal distribution. Enumerated data will be displayed in percentage. For the primary outcome, we will calculate the IGA score at 8 weeks, and use the χ^2^ test to compare group A and group B. For secondary outcomes, continuous variables including IGA, TCL, Inflammatory lesion count, Non-inflammatory lesion count, Qol-Acne, and the Expectation and Credibility of acupuncture treatment will be compared at 8 and 12 weeks, using an unpaired Student *t* test or Wilcoxon rank-sum test (depending on the situation). A *P* value of <.05 will be considered a limit of statistical significance.

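### The sample size rests on an undefined effective rate with no stated link to the IGA primary outcome or its test, so the power for that outcome is undetermined

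*Protocol article*

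**What the plan says.** Section 2.5.2 (Sample size) takes two rates as its effect assumption. From literature on ordinary acupuncture, "the average effective rate was 76.7" per cent. From clinical experience, "the total effective rate of SSGA in treating acne is 98.48" per cent. The effect size is their difference, "0.9848-0.767 = 0.2178", with "One-sided cutoff of this trial: z_α_ = 1.645" and z_β = 1.282. This gives about 32, raised to 38 per group for dropout, hence 76.

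The outcome sections describe something else. Section 2.4.1 (Primary outcome): "The primary outcome measurement will be expressed by the change in IGA score from baseline to the end of 8-week treatment". IGA is graded 0 to 5. The abstract puts it slightly differently: "The primary outcome is the investigation global assessment (IGA) at week 8". Section 2.5.1 (Clinical data analysis) gives the primary test: "For the primary outcome, we will calculate the IGA score at 8 weeks, and use the χ^2^ test to compare group A and group B". The same section lists IGA among the continuous secondary variables, to be compared by t test or Wilcoxon rank-sum test. The secondary outcomes in section 2.4.2 are changes in IGA, lesion counts and acne-specific quality of life. None of them is an effective rate.

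**The concern.** The quantity that fixes the sample size should be the quantity that the primary analysis tests. Here three sections point three ways: a difference in rates (2.5.2), a change in an ordinal score (2.4.1), and a chi-square test on a score with no stated grouping (2.5.1). Nothing converts one into another. The literature rate and the clinical-experience rate are not tied to any IGA threshold, so a reader cannot tell what IGA result they correspond to.

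Two things are at stake. First, the only justification for 76 patients does not concern the primary outcome. Second, the abstract says that the results will feed sample-size calculations for larger studies. The observed IGA result cannot be set against the planning assumption, because the two are on different scales.

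**Working it through.** **1. Reproduce the plan's figure.** Inputs from section 2.5.2: π₀ = 0.767, π = 0.9848, δ = 0.2178, z_α = 1.645, z_β = 1.282.

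n = π₀(1 − π₀) × [(z_α + z_β)/δ]² = 0.767 × 0.233 × (2.927/0.2178)² = 0.17871 × 180.60 = 32.28, stated as about 32. Then 32 × 1.2 = 38.4, stated as 38 per group, and 2 × 38 = 76. The arithmetic reproduces, and no IGA quantity enters it. Power is not written in words; z_β = 1.282 corresponds to 90%.

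**2. Look for a link from the rates to IGA.**

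| Section | Quantity | Scale |
|---|---|---|
| 2.5.2 | Effective rate, undefined | Proportion |
| 2.4.1 | Change in IGA to week 8 | Score |
| 2.5.1, primary | Week-8 IGA, chi-square | Categorical, grouping not stated |
| 2.5.1, secondary | IGA, t test or Wilcoxon | Continuous |

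No section supplies a cut-off.

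**3. What 76 patients give for change in IGA.** Two-sided 5% t test, noncentral t distribution with 2n − 2 degrees of freedom. Thirty per arm is not a protocol figure; it assumes that 20% of 38 are lost (38 × 0.8 = 30.4).

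| Per arm | Detectable at 80% | Detectable at 90% |
|---|---|---|
| 38 | 0.65 SD | 0.75 SD |
| 32 | 0.71 SD | 0.82 SD |
| 30 | 0.74 SD | 0.85 SD |

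Turning these into IGA grades needs an SD, which the article does not give. For an assumed range of 0.6 to 1.2 grades, 0.75 SD is 0.45 to 0.90 grade.

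Power for an assumed difference Δ, by normal approximation, is Φ(Δ/(SD × √(2/n)) − 1.96). With n = 38 and Δ = 0.5 grade:

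| Assumed SD | Power |
|---|---|
| 0.6 | 95% |
| 0.8 | 78% |
| 1.0 | 59% |
| 1.2 | 44% |

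The noncentral t gives values up to about one percentage point lower. Widening the assumed Δ to 0.3–0.75 grade, power runs from 19% (Δ 0.3, SD 1.2) to over 99% (Δ 0.75, SD 0.6).

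**4. What 76 patients give if the rates did describe an IGA responder.** The formula in step 1 compares one sample with a fixed population rate, so a two-arm comparison has to be recomputed. With p̄ = (0.767 + 0.9848)/2 = 0.8759:

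power = Φ{[δ − z_α√(2p̄(1 − p̄)/n)] / √([π₀(1 − π₀) + π(1 − π)]/n)}

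For n = 38, one-sided: (0.2178 − 1.645 × 0.0756)/0.0714 = 1.31, so 90%.

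| Per arm | One-sided 5% | Two-sided 5% |
|---|---|---|
| 38 | 90% | 84% |
| 32 | 85% | 77% |

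These are approximations, and with a rate near 98% they are rough: 32 × (1 − 0.9848) is about 0.5 expected non-responders in the SSGA arm. Exact enumeration, two-sided, gives 86% for an uncorrected chi-square test and 65% for Fisher's exact test at 32 per arm, and 92% and 79% at 38 per arm.

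**The case against.** The best defence is that the planned primary test is a chi-square test. That is a categorical analysis, and sizing on rates belongs to the same family. On this view IGA was always meant to be dichotomised, and the responder rule sits in a fuller document that is not shown. Part of this stands. A reader might infer that the sized endpoint will never be measured or tested; the article does not support that, since week-8 IGA is recorded and tested categorically, and what is missing is the rule linking it to the rates. But the defence does not remove the point. Section 2.4.1 names a change in score as primary, section 2.5.1 elsewhere treats IGA as continuous, and the two rates come from sources not tied to any IGA threshold. These are statements within the article that do not fit together, not detail left out for brevity.

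A reader might also infer that the trial is underpowered or has less than 90% power. The documents do not show that. With no SD or target difference, the power for change in IGA could be well below or well above 90%. The t-test figures also describe an analysis that section 2.5.1 does not now assign to the primary outcome; they show what the first remedy below would have to state.

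Finally, the trial describes its efficacy aim as preliminary and admits that its sample is small. That argues against asking for more patients. It does not excuse a formal calculation that concerns a different quantity from the primary outcome.

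**Conclusion.** The point holds in this form: 76 patients and the implied 90% power follow from an effective rate that the article neither defines nor connects to its IGA primary outcome or to the chi-square test. The arithmetic is reproducible, but its result does not carry over. Power for the primary outcome is undetermined. If change in IGA is analysed by a two-sided 5% t test, the trial detects 0.65 to 0.74 SD at 80% power and 0.75 to 0.85 SD at 90%, over 38 down to 30 evaluable per arm. Any translation into IGA grades rests on an SD that has to be assumed. If instead the two rates are taken as IGA responder rates, two-sample power by normal approximation is 77% to 90%, depending on sidedness and on whether 32 or 38 per arm are evaluable.

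**What to change.** Keep 76 patients and make sections 2.4.1, 2.5.1 and 2.5.2 describe one endpoint, in one of two ways.

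**(a) Change in IGA stays primary.** In 2.5.1 replace the chi-square test by a test suited to a score change; the t test and Wilcoxon test are already named there. In 2.5.2 replace the effective-rate calculation by the detectable difference from step 3, with the number evaluable and the assumed SD of IGA change stated. Rewriting 2.5.2 alone would leave the chi-square test in conflict with the new sizing.

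**(b) An IGA responder at week 8 becomes primary.** Define it in 2.4.1, keep the chi-square test, justify both rates for that definition, and restate the power for a two-sample comparison with its sidedness. A definition alone is not enough, because the present rates were not derived for it.

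The cost is modest: a rewritten sample-size paragraph, plus the matching sentences in the other two sections, with no added visits. The stated power may become less favourable. Under (b), with the present rates, holding 90% by normal approximation would need 38 evaluable per arm one-sided or 47 two-sided, so at 76 randomised the sponsor would report the lower power instead.

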### Quality control and safety monitoring

2.6

To promote patient retention and complete follow-up, total interventions to patients are free of charge. The data relating to this study will be recorded in the CRFs, and then input into the Excel spreadsheet by independent investigators as the first level of control to guarantee the accuracy of the data. The second level of data integrity will include data integrity validation and data monitoring throughout the study carried out regularly. All original forms (including the consent forms and CRFs) will be safely stored in Dongzhimen Hospital of Beijing University of Chinese Medicine. The Research Ethics Committee of Dongzhimen Hospital of Beijing University of Chinese Medicine will audit the trial independently of the investigators every 5 months and will decide whether to end the study early.

From baseline to week 12, adverse events and their numbers will be recorded. These adverse events will include adverse events related to acupuncture, such as needle fainting, infection, hematoma, sensation after acupuncture, as well as adverse reactions that cannot be related to acupuncture. For the safety assessment, the trial assistant will record the details of all adverse events in the CRF. Any serious adverse event will be reported to the ethical committees of Dongzhimen Hospital of Beijing University of Chinese Medicine within 24 hours, and the Dermatology Department will compensate for any injuries related to the intervention during the study period. The specific trial intervention process is shown in Figure 3 below.

**Figure 3 F3:**
[figure not shown]
Template of content for the schedule of enrolment, interventions, and assessments. AFT = after the first treatment, TLC = total lesion count, IGA = investigation global assessment, Acne-Qol = acne-specific quality of life questionaire.

